#### 2.3.4. Randomization

Participants (*n* = 48) will be randomly assigned 1:1:1:1 to the following groups: (1) TRE; (2) Mindfulness; (3) TRE and Mindfulness; or (4) Control. We will use a stratified randomization approach considering sex (female vs. male) to ensure balance across treatment arms. Randomization will occur after all aspects of the baseline data collection are completed.

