#### 2.6.7. Microbial Amplicon Sequencing and Bioinformatics Processing

16S rRNA amplicon sequencing will be performed using microbial DNA extracted from participant stool samples. Sample preparation and analysis will be conducted by the University of Illinois Genomics Core. The V4 region of the 16S rRNA gene will be amplified and sequenced with the Illumina MiniSeq platform (Azenta Life Sciences, Burlington, VT, USA). Environmental controls will be included in the sequences to distinguish any contaminants. Moreover, 16S rRNA reads will be processed with DADA2 (version 3.11) [47] to identify the number of counts of amplicon sequence variants (ASVs). ASVs with a low number of counts or with a low abundance (<1%) will be removed from downstream analysis. ASVs will be summarized at different phylogenetic levels and normalized using cumulative sum scaling [48]. Variation in community structure alpha (i.e., Shannon) [49] and beta diversity (e.g., Bray-Curtis distances) [50] in response to the intervention will be determined within and between groups with the vegan [51] and phyloseq [52] packages in R (R Foundation for Statistical Computing, Vienna, Austria). Compositional differences will be determined using zero-inflated generalized liner mixed models correcting for covariates (e.g., BMI, sex, age) using MaAsLin2 (version 3.18) [48,53].

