Exploratory inferential statistics will be conducted, but no conclusions on the efficacy of the interventions will be drawn from the results. Initially, we will evaluate distributions, identify any outliers, and look for patterns of missing data. The continuous endpoints (stress, body weight, body composition, and cardiometabolic health) will be estimated among each of the groups, and the 95% confidence interval will be constructed assuming normal distribution, respectively. Then, a two-sample *t*-test will be utilized to compare each of the three intervention groups and the control group. GLM will be employed to estimate the adjusted difference in each of the continuous endpoints between the different groups. We will also investigate co-primary (body, weight, objective stress markers) and secondary outcomes (i.e., body composition, PSS, cardiometabolic measures) for between- and within-treatment differences and test for (treatment) × (time) interactions to compare the trends over time using generalized linear mixed models. We will investigate changes in microbial community diversity and composition (ASVs), tryptophan-related metabolites, and systemic and intestinal inflammation changes from baseline to post-intervention by treatment arm. The other binary endpoints will be compared between the different groups using Fisher’s exact test or chi-square test, respectively. Multivariate logistic regression will be further employed to compare these binary endpoints between the different groups, after adjusting for plausible confounders. Odds ratios and 95% confidence intervals will be calculated to evaluate the strength of any association that emerges.

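### Randomisation is stratified by sex but the stated between-arm t-test ignores it, so the t-test is conservative for endpoints that depend on sex and are compared as post-intervention values (minor)

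*Protocol article*

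**What the plan says.** Section 2.3.4 (Randomization) names one stratification factor, sex, and gives its purpose: "We will use a stratified randomization approach considering sex (female vs. male) to ensure balance across treatment arms". The 48 participants "will be randomly assigned 1:1:1:1 to the following groups", so 12 per arm. No block scheme is described.

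Section 2.7 (Data Analytic Plan) takes up the continuous endpoints: "The continuous endpoints (stress, body weight, body composition, and cardiometabolic health) will be estimated among each of the groups". The stated comparison follows: "a two-sample *t*-test will be utilized to compare each of the three intervention groups and the control group". The next sentence adds a model-based analysis: "GLM will be employed to estimate the adjusted difference in each of the continuous endpoints between the different groups". Its covariates are not listed. Mixed models with a treatment-by-time term are planned as well. The text does not say whether the t-test is run on post-intervention values or on changes from baseline.

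Sex is named as a covariate in one place only, as an example for the microbiome composition models in Section 2.6.7: "correcting for covariates (e.g., BMI, sex, age) using MaAsLin2".

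Two statements bear on how much this matters. Section 2.6.12 says that the sample supports confidence intervals for feasibility and for effect sizes. Section 2.7 says that the inferential tests are exploratory and will support no conclusion on efficacy.

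**The concern.** Stratifying by sex takes most of the sex imbalance out of the arm difference, so the true variance of that difference falls. A two-sample t-test cannot see this. Its pooled SD contains the spread between men and women as well as the spread within each sex, and all of it enters the standard error. The interval is then wider than the design warrants, and the test rejects a true null hypothesis less often than its nominal rate.

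The loss depends on how strongly the endpoint depends on sex. Weight and lean mass compared as post-intervention values are the plausible cases. With about 10 completers per arm expected, the effect-size intervals are wide already, and they are one of the products that the pilot is meant to hand to the larger trial.

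**Working it through.** **The plan's own figure.** Section 2.6.12 gives a minimum detectable difference of 1 SD for n = 10 per arm, r = 0.5, alpha 0.05 and 80% power, between baseline and post-intervention. The SD of a change is sqrt(2 × (1 − 0.5)) = 1 SD. A paired t-test with n = 10 and two-sided alpha 0.05 has 80.3% power at 1 SD and a detectable difference of 0.996 SD. The figure reproduces, as a within-arm figure. It does not describe the between-arm t-test, and sex plays no part in it.

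**Inputs for the check.** From the protocol article: N = 48, four equal arms, stratification by sex, 40 completers (8/48 = 16.7% loss) and alpha 0.05. Assumed, because the article does not give them: male share p of 15%, 30% or 50%, and a male-female difference d of 0.3, 0.8, 1.5 or 2.0 within-sex SDs.

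**Formula under exact balance.** The true variance of the arm difference uses the within-sex variance, 1. The t-test uses approximately 1 + p(1−p)d². Its standard error is therefore too large by the factor sqrt(1 + p(1−p)d²):

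- p = 0.15: d = 0.8 gives sqrt(1 + 0.1275 × 0.64) = 1.04; d = 2 gives sqrt(1.51) = 1.23.
- p = 0.25: d = 1 gives sqrt(1.1875) = 1.09; d = 2 gives sqrt(1.75) = 1.32.
- p = 0.50: d = 0.8 gives sqrt(1.16) = 1.08; d = 2 gives sqrt(2) = 1.41.
- d = 0.3: between 1.006 (p = 0.15) and 1.011 (p = 0.50).

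**Simulation with imperfect balance.** Permuted blocks of 4 within sex, 17% random dropout, one arm against control, no treatment effect, 8,000 runs per row (Monte Carlo standard error about 0.24 percentage points at 5%). The SE ratio is the t-test's standard error over the true one. The width ratio is the t-test interval over the interval from a model with arm and sex.

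| Men | d | Type I error, t-test | Type I error, arm + sex | SE ratio | Width ratio |
|---|---|---|---|---|---|
| 15% | 0.3 | 4.90% | 4.99% | 1.004 | 0.993 |
| 15% | 0.8 | 4.05% | 4.69% | 1.037 | 1.028 |
| 15% | 1.5 | 3.50% | 5.00% | 1.100 | 1.128 |
| 15% | 2.0 | 2.80% | 5.44% | 1.157 | 1.224 |
| 30% | 0.3 | 4.61% | 4.84% | 1.018 | 0.999 |
| 30% | 0.8 | 4.10% | 4.75% | 1.066 | 1.057 |
| 30% | 1.5 | 2.79% | 5.01% | 1.151 | 1.216 |
| 30% | 2.0 | 1.52% | 4.66% | 1.248 | 1.363 |
| 50% | 0.3 | 4.61% | 4.81% | 1.012 | 1.001 |
| 50% | 0.8 | 3.82% | 5.19% | 1.055 | 1.071 |
| 50% | 1.5 | 2.20% | 5.05% | 1.207 | 1.257 |
| 50% | 2.0 | 1.21% | 4.98% | 1.296 | 1.427 |

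**Sensitivity at 30% men.** Blocks of 8 give 4.04% (d = 0.8) and 2.46% (d = 1.5). Blocks of 4 without dropout give 3.81% and 1.88%. If allocation were not restricted within sex, the t-test would hold its level (5.22% and 4.98%), so the conservatism comes from the balancing.

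**The case against.** The best answer is that the plan already contains the remedy. The sentence after the t-test promises an adjusted GLM for the same endpoints, and an article may leave its covariate list to the analysis plan, which is not shown. This stands in part. A reader might infer that sex has been left out of the GLM. The article does not support that: it names no GLM covariates at all, and silence is not exclusion. What remains is that the t-test is itself a stated comparison, that it cannot use sex, and that the article does not say which estimate will be reported.

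Second, the size rests on assumptions. A sex gap of 1 to 2 SDs is arguable for post-intervention weight or lean mass, but nothing in the article supports such a gap for changes, or for perceived stress. A stable sex difference cancels from a change score and from a treatment-by-time term. This stands. A reader might infer that every between-arm interval is too wide. That holds only for endpoints that depend on sex in the form in which they are compared.

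Third, exact balance is not guaranteed, since no block scheme is given. The simulation with blocks and dropout softens the effect but does not remove it, and balance is the stated aim of the stratification.

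Fourth, feasibility and acceptability are the primary outcomes and are untouched, the tests are exploratory, and power for comparisons between groups is expressly not claimed. This stands and limits the severity.

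**Conclusion.** The point holds in a conditional form and is minor. The stated t-test does not use the factor by which the trial is stratified. For an endpoint that depends on sex by 0.8 to 2 within-sex SDs and is compared as a post-intervention value, with 15-50% men and allocation that really balances sex, the t-test's standard error is about 4-30% too large. Its real type I error is about 4% down to 1% instead of 5%. At 0.3 SD or less, as may apply to changes or baseline-adjusted values, type I error is 4.6-4.9% and the interval width is practically unchanged.

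The error is in the conservative direction. It leads to no false claim of efficacy, because the plan draws no efficacy conclusions. Its cost is over-wide effect-size intervals for planning the next trial.

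A reader might also infer that the SDs passed to the larger trial are overstated. The article does not say which SD will be passed on. The pooled SD is a fair estimate of the SD with both sexes together, and is too large only for planning an analysis that adjusts for sex.

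**What to change.** Include sex as a fixed effect, with the endpoint's baseline value where it is used, in the GLM or mixed model already planned for the continuous endpoints. Report the arm differences and 95% confidence intervals from that model instead of from the unadjusted t-test. If the analysis plan already lists sex as a covariate, all that is needed is to state that the model estimate is the one reported.

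The change costs one line of text and one degree of freedom, and needs no new data, since sex is known for everyone at randomisation. Where sex has no effect, the adjusted interval was only about 1% wider in the simulation (width ratio 0.987 to 0.990). Where d was 0.8 or more, type I error with sex in the model was 4.7-5.4%, and the t-test interval was 3-43% wider than the adjusted one.

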### 2.4. Interventions

The intervention sessions will be conducted remotely via videoconferencing (i.e., Zoom).

#### 2.4.1. Time-Restricted Eating (TRE)

Participants will be instructed to eat ad libitum from 12:00–8:00 p.m. daily and fast during the remaining hours (16-h fast). The set eating window was selected based on an observational study of 800,000 North Americans, which found that individuals usually place their TRE eating window from 12–8 p.m. so that they can have lunch and still eat dinner with friends and family [44]. During the 8-h eating window, there will be no restrictions on the types or quantities of foods consumed. In addition, participants will not be required to monitor calorie intake. During the fasting period, participants will be encouraged to drink plenty of water and consume energy-free beverages only, such as black tea or coffee. Participants will meet with a registered dietitian for 30 min at the start of the intervention to review instructions and goals and weekly thereafter. Weeks 2–8 will focus on TRE adherence and personalized problem solving related to adherence to the TRE intervention. Each day, participants will respond to a text message to indicate their eating start and stop times. If the message indicates that the participant ate only within the prescribed eating window (±30 min of 12 p.m. and + 30 min of 8 p.m.), that day will be labeled “adherent”, otherwise the day will be labeled “non-adherent.” On the same day and time each week, participants will be asked to transmit a picture of their weight from a home scale via a secure text-messaging platform. Participants will be asked to maintain their baseline level of physical activity.

#### 2.4.2. Mindfulness

Participants in this study will be granted access to the Calm.com [45] platform. Calm.com (https://www.calm.com, accessed on 22 January 2024) is a subscription-based software application to promote positive mental health [45]. Participants will have access to the “Mindfulness for Beginners” course, consisting of 30 audio lessons, each ranging from 9 to 14 min long. The title of each session is described in Table 2. During the study, participants will be asked to complete four sessions per week during weeks 1–7 and two lessons during week 8. Research staff will provide participants randomized to the Mindfulness arm with instructions on how to access the platform and a tutorial on how to navigate and engage with digital intervention. Participants will be asked to transmit a picture of their course progress via a secure text-messaging platform on the same day and time each week. 

Staff will monitor weekly usage and contact participants who engage with sessions outside of the intended protocol (i.e., less than or more than four sessions per week for weeks 1–7 of the "Mindfulness for Beginners" course) to optimize and standardize engagement. Research staff will contact participants assigned to this group weekly to track engagement in the study and answer any questions they may have. Participants will be asked to maintain their baseline level of physical activity.

#### 2.4.3. TRE and Mindfulness

This group will follow a combined protocol of the TRE and Mindfulness as described above. Participants will be asked to maintain their baseline level of physical activity.

#### 2.4.4. Control

The control group will not receive any of the interventions described. To maintain a relationship with each participant in the control group, we will contact them once a week via phone. Participants will be asked to maintain their baseline level of physical activity. At the end of the intervention period, and after all data is collected, the registered dietitian will meet with the participants for 30 min and educate them regarding the TRE protocol and provide access to the Calm.com platform. 

### 2.5. Intervention Fidelity

To assure the fidelity of the TRE intervention sessions, the content is semi-structured in a flexible format. Given the individualized nature of the sessions, the interventions cannot be fully scripted. A semi-structured approach will allow for the use of a fidelity checklist itemizing the expected general content of sessions. Non-interventionist staff ([name] ([name])) will be randomly selected to observe and complete the fidelity checklist. When necessary, [name] will meet with interventionists to provide feedback from the fidelity checklist and to address deviations from the intended intervention content.

### 2.6. Data Collection and Measures

Data collection will occur at baseline and post-intervention. The following measures will be collected at both time points, unless stated otherwise:

#### 2.6.1. Body Weight and Body Composition

Body weight will be measured in a fasted state to the nearest 0.1 kg using a calibrated digital scale (Tanita BWB-800, Arlington Heights, IL, USA). Body composition will be measured by dual-energy X-ray absorptiometry (iDXA, GE Healthcare, Chicago, IL, USA) at baseline and post-intervention. Height will be measured at screening using a fixed stadiometer (Seca, Hamburg, Germany). BMI will be calculated as weight (kilograms)/height (meters squared) from screening height and measured body weights.

#### 2.6.2. Dietary Intake

We will collect two 24-h diet recalls at each time point using the Automated Self-Administered 24-h Dietary Assessment Tool (ASA-24) (US National Cancer Institute, Bethesda, MD, USA). The 24-h food recall is necessary to collect information about the participant’s diet from the previous day during a set 24-h period, 12:00 a.m. to 11:59 p.m. We will collect dietary data to explore any changes in caloric intake, diet patterns, and macro- and micronutrient intake across the study arms. At baseline, the participant will self-administer the first food recall in person during the baseline data collection. This will allow the research staff to answer any relevant questions and the participant to learn how to successfully complete this questionnaire. Participants will be asked to self-complete the second food recall 2–4 days after the baseline data collection. The third food recall will be self-completed 2–4 days prior to the participant’s post-intervention data collection. The fourth food recall will be self-completed during the post-intervention data collection visit. 

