Time-Restricted Eating (TRE) may be a salient and effective approach to weight management and EOCRC prevention among individuals with obesity and CPS. TRE is a popular type of intermittent fasting that produces a ~300–500 kcal daily energy deficit by simply limiting an individual’s eating window to 4–8 h each day [23]. Individuals following TRE are asked to limit food intake to a specified time frame (e.g., 12 p.m.–8 p.m.) and no-calorie fast (i.e., only consume water or zero-calorie beverages) for the remaining hours of the day. Studies of TRE in humans show high adherence among both younger and older adults with obesity and clinically meaningful weight loss (over >5% weight loss). Moreover, TRE is associated with improvements in insulin sensitivity, systemic inflammation, oxidative stress, circulating insulin-like growth factor 1, and leptin, indicating its potential applicability for preventing EOCRC [24,25,26]. Given its simplicity, TRE may also be more acceptable for weight management among individuals with CPS compared to traditional calorie restriction given that TRE does not require individuals to count calories and continuously monitor their intake, which may serve as an additional stressor. 

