### 2.3. Participants

#### 2.3.1. Screening

Individuals interested in participating will first complete a survey to assess eligibility using a link shared via email. If an individual meets the basic inclusion criteria, they will be invited to an in-person screening to complete informed consent. They will be asked to fast for 12 h prior to their in-person screening. Individuals will be weighed using an electronic scale, and height will be assessed with a fixed stadiometer to confirm BMI (kilograms per meters squared). Individuals meeting all screening metrics (Table 1) will be invited to participate in the full trial. If the participant is eligible based on their height and weight, arrived after fasting for 12 h, and is interested in continuing in the study, baseline data collection will immediately commence. 

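### One of the two diet recalls at each time point covers the day before a 12-h fasting visit; with morning visits this probably attenuates the exploratory contrast in intake change under TRE

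*Protocol article*

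**What the plan says.** Protocol article, section 2.6.2 (Dietary Intake): "We will collect two 24-h diet recalls at each time point". Each recall asks about the participant's "diet from the previous day during a set 24-h period, 12:00 a.m. to 11:59 p.m".

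The four recalls are placed as follows:
- Recall 1: "At baseline, the participant will self-administer the first food recall in person during the baseline data collection".
- Recall 2: "Participants will be asked to self-complete the second food recall 2–4 days after the baseline data collection".
- Recall 3: at home, 2–4 days before the post-intervention visit.
- Recall 4: "The fourth food recall will be self-completed during the post-intervention data collection visit".

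Section 2.3.1 (Screening) says of participants: "They will be asked to fast for 12 h prior to their in-person screening". If they are eligible and arrive fasted, baseline collection starts at once, in the same visit. Section 2.6.4 specifies 12-h fasting blood, and section 2.6 applies its measures to both time points, so the post-intervention visit is also a fasting visit. Section 2.4.1 sets the TRE eating window at noon to 8 p.m. The stated purpose of the dietary data is to explore changes in calories, diet patterns and nutrients across the arms. The article gives no clock time for the visits.

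**The concern.** The visit instruction and the intervention act on the same behaviour. A 12-h fast before a morning visit stops eating on the previous evening, which is part of what TRE asks for. Recalls 1 and 4 record exactly that evening.

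In an arm whose evening eating does not change, the fast lowers both time points alike and drops out of the change score. In the TRE arms it lowers the baseline value. It removes little from the post-intervention value, because by then evening eating has already stopped. The distortion therefore need not cancel between arms, and a larger sample would not reduce it.

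What is at stake is an exploratory result. Even so, the introduction's rationale for TRE is that it "produces a ~300–500 kcal daily energy deficit", and the recalls are the trial's direct look at that deficit. The pilot also exists partly to test data-collection methods for a larger trial, so a weakness in the recall schedule could be carried forward.

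**Working it through.** **The plan's own figure.** The article states no figure for dietary intake. Its only power statement (section 2.6.12) is a minimum detectable within-arm change of 1 SD with n = 10 per arm, r = 0.5, alpha 0.05 and 80% power. It reproduces: the SD of change is SD × √(2 × (1 − 0.5)) = 1 SD, and a two-sided paired t-test with n = 10 gives 0.996 SD, with 80.3% power at 1 SD. The present point does not depend on it.

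**Inputs from the article.** Two recalls per time point, one of them at the fasting visit; a recall day from midnight to 11:59 p.m.; a 12-h fast; TRE eating ending at 8 p.m.; a TRE deficit D of about 300–500 kcal/day, used only as an illustration.

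**Assumptions not in the article.**
- V = visit hour on the 24-h clock.
- e = share of D that comes from no longer eating after 8 p.m. The rest comes mainly from not eating before noon.
- Eating after 8 p.m. is spread evenly up to midnight.
- Evening intake given up for the fast is not eaten earlier that day.
- TRE participants keep to the 8 p.m. stop at post-intervention.

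**Step 1: how much of the evening the fast closes.** The fast starts at hour V + 12 of the previous day. The fraction of the four hours from 8 p.m. to midnight that it closes is f = (24 − (V + 12))/4 = (12 − V)/4, limited to between 0 and 1. Thus f = 1 at 8 a.m. or earlier, 0.75 at 9 a.m., 0.5 at 10 a.m., 0.25 at 11 a.m., and 0 at noon or later.

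**Step 2: recorded change.** Let B be usual intake.
- TRE baseline mean of two recalls: B − ½·e·f·D.
- TRE post-intervention mean: B − D.
- TRE recorded change: −D + ½·e·f·D = −D(1 − e·f/2).
- Control with stable intake: both means fall by the same amount, so the change is 0.
- Share of the contrast lost: e·f/2.

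**Step 3: numbers.**

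| Visit | f | e = 0.25 | e = 0.5 | e = 1 |
|---|---|---|---|---|
| 8 a.m. or earlier | 1 | 12.5% | 25% | 50% |
| 9 a.m. | 0.75 | 9.4% | 18.8% | 37.5% |
| 10 a.m. | 0.5 | 6.25% | 12.5% | 25% |
| 11 a.m. | 0.25 | 3.1% | 6.25% | 12.5% |
| Noon or later | 0 | 0% | 0% | 0% |

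For a visit at 8 a.m. or earlier and D = 300–500 kcal/day, the loss is 37.5–62.5 kcal/day at e = 0.25 and 75–125 kcal/day at e = 0.5. If no analysed recall covers a pre-fast day, the loss is 0.

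**The case against.** A reader might infer that the plan understates the fall in intake under TRE, and by as much as half. The article does not support that.

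- **Visit time.** No visit hour is given. The coincidence with the 8 p.m. stop needs a visit at about 8 a.m. For a visit at noon or later the fast does not reach the previous calendar day.
- **Compensation.** Someone told to stop early may eat a larger or earlier dinner, which the same recall records. Full compensation would remove the bias in total energy. Recorded eating times would still shift, but the article plans no eating-window measure from the recalls.
- **Post-intervention value.** For a visit before 8 a.m. the fast also cuts into the TRE window, and a TRE participant who still eats late is also affected at recall 4. In both cases part of the bias may cancel.
- **The 50% figure.** It requires the whole deficit to come from after 8 p.m. and none from before noon, although the window opens only at noon.
- **Importance.** Intake is exploratory and is not among the primary or secondary outcomes listed in the introduction. TRE adherence comes from daily text messages (section 2.4.1). Section 2.7 rules out efficacy conclusions.
- **Trade-off.** The in-person first recall has a stated purpose: staff can answer questions and the participant learns the tool.

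All of this stands, and it limits the certainty, size and importance of the point. It does not remove the overlap itself, which follows from the article's own schedule, or the reason why the overlap need not cancel between arms.

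**Conclusion.** The point holds in conditional form. It is certain from the article that recalls 1 and 4 each cover the day before a 12-h fasting visit, in all four arms, and that recalls 2 and 3 do not. Given morning visits, incomplete compensation and adherence to the 8 p.m. stop, the contrast in intake change between the TRE arms and control is probably attenuated.

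The article does not allow the amount to be fixed. It ranges from 0 for visits at noon or later to an illustrative 12.5–25% for visits at or before 8 a.m., when a quarter to a half of the deficit comes from after 8 p.m. The consequence is confined to exploratory dietary results. It is worth correcting because the remedy is cheap and the pilot is meant to inform the methods of a larger trial.

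**What to change.** Keep the in-person baseline recall, but use it as the training recall only. Take both analysed baseline recalls in the seven-day Fitbit week after the visit. This is still before randomisation, because section 2.3.4 places randomisation after all baseline collection. Take both analysed post-intervention recalls in the seven-day Fitbit week before the post-intervention visit. No analysed recall should cover the day before a fasting visit. A baseline recall completed on the day after the visit should also be avoided, since it would cover the fasted morning of the visit day.

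The cost is one extra self-administered recall at baseline (five in total instead of four); recall 4 is only moved. No staff would be present for the analysed recalls, and the extra recall counts toward the target of completing at least 80% of planned assessments.

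If the schedule cannot change, record the visit times and prespecify a sensitivity analysis of intake change on recalls 2 and 3 alone. This needs no new data beyond the visit times, but it leaves one day per time point instead of two and so loses precision.
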